Thrombectomy provision is currently expanding in many countries. In the UK, regional neuroscience ‘hubs’ will provide this treatment for populations of 1.5–3 million. The majority of eligible patients will initially be identified at local Hyperacute Stroke Units (HASU) ‘spokes’ which serve populations of 0.3–1 million. Due to the expertise and facilities required, thrombectomy cannot be provided at every HASU and will only be available in 25 out of 126 sites admitting stroke across England, Wales and Northern Ireland [13]. In this service arrangement, patients presenting at local HASU’s with ischaemic stroke that appear potentially suitable for thombectomy on the basis of clinical stroke severity (NIHSS > 5), radiological criteria and previous medical history will need to undergo additional local CT angiography or MR angiography to confirm the presence of LVO before transfer onto the regional neuroscience hub. This assessment process takes at least one additional hour relative to direct admission to a regional neuroscience hub [14]. In addition, CT/MR angiography is not yet routinely available at all local HASUs in the NHS, and patients admitted to these sites may not be offered thrombectomy treatment as LVO cannot be identified.

Thrombectomy treatment rate and speed would be much improved if patients with LVO stroke could be identified sooner. If this could be done in ambulances, it would enable transportation directly to a regional neuroscience centre. However, reducing the need for additional CT/MR angiography at a local HASU would also be of benefit. In terms of pre-hospital detection of LVO, paramedic completed clinical assessments have been developed to identify LVO stroke patients, but their performance in practice does not support widespread introduction [15].

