### Reference standards

Reference standard tests are required for key outcome states which constitute the suspected stroke population: large volume intracerebral haemorrhage (LICH), small/medium intracerebral haemorrhage, ischaemic stroke with LVO (LVO), ischaemic stroke without LVO, symptomatic severe anterior vessel stenosis (SSAVS), transient ischaemic attack (TIA), mimic conditions and prior territorial stroke (PTS). In clinical practice, some of the acute outcome states can overlap (e.g ischaemic stroke or TIA can be caused by SSAVS), and all acute outcome states may co-exist with a prior territorial stroke. As only one outcome state can be allocated for study analyses, non-overlapping discrete definitions and reference standards have been assigned for each acute outcome state and an attribution process developed to describe when PTS will be the state assigned. The definitions and attribution process result in the presence of any ‘complex stroke’ (i.e. ischaemic stroke with LVO or SSAVS or LICH ≥ 60 ml in volume or PTS) being dominant over other states which are in keeping with the intended purpose of the CVS test.

Whilst brain imaging tests are available which objectively confirm any intracerebral haemorrhage (CT), LVO (CT/MR angiography), and PTS (CT), no single diagnostic test exists for ischaemic stroke without LVO, SSAVS, TIA and mimic conditions. For SSAVS, the reference standard will be based on brain imaging plus clinical report of the side of the body affected by focal neurological symptoms. For ischaemic stroke without LVO, TIA and mimic conditions, the reference standards will be based on expert clinician diagnosis informed by brain imaging +/− other investigations as clinically appropriate. Full details are given below and a summary of the reference standards to be used is shown in Table 1.

**Table 1 Tab1:** Summary of clinical outcome states and their reference standards

	Outcome state	Reference standard
Complex	Ischaemic stroke with large vessel occlusion	CT/MR angiography assessed by blinded neuro-radiologist. LVO defined as a Ten Point Clot Burden Score <10.
	Large volume intracerebral haemorrhage	Brain imaging assessed by blinded neuro-radiologist. Haematoma volume of at least 60ml in a single cerebral hemisphere.
	Prior territorial stroke	Brain imaging assessed by blinded neuro-radiologist. Appropriate changes in either cerebral hemisphere.

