This is an exploratory objective, and as such the analyses will be data-driven and dependent on results for objectives 1 and 2. Proposed investigations focus on three main areas: (i) whether available clinical data might be incorporated to improve the diagnostic accuracy of the CVS; (ii) variations in specification of the reference diagnosis for LVO, and (iii) patient subgroup analyses to identify whether the CVS may perform better in some clinical settings than others.
(i)Clinical covariates: key variables will be added to the logistic regression models described in objectives 1 and 2 to see if this could significantly increase the accuracy of the prediction of the model. Clinical variables that would be available to ambulance personnel or staff involved in urgent assessment at the hospital will be included to reflect those available at the point of testing. Multivariate logistic regression will be conducted, with diagnosis (complex stroke OR LVO) as the outcome (*y*) and CBA measurement along with variables considered to be of possible clinical importance (such as gender, age, NIHSS) as the explanatory variables (*x*1, *x*2, *x*3, …). A stepwise variable selection procedure will be used, and only variables that significantly improve the ROC AUC will be retained in the model. Sensitivity, specificity, ROC AUC (with confidence intervals) and threshold will be reported if a suitable model is found.(ii)Alternative definitions for LVO: the diagnostic accuracy of CBA measurement will be assessed by modelling as described for objective 1, where the reference diagnosis will be assigned as follows:

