Radiological definition: At the time of the data analysis, if the clinical consensus regarding size and distribution of clot that is feasible for thrombectomy (described using the clot burden score and/or the extended TICI scale) has changed, the alternative definition(s) will be used to re-categorise participants as LVO present or absent.Best clinical standard for LVO identification: currently, the most accurate clinical scale for the indication of the presence of LVO is the Rapid Arterial oCclusion Evaluation (RACE) [31]. A numerical RACE score will be calculated retrospectively using the hospital NIHSS (which contains all score items), as RACE is not routinely in use in the UK and will not be used in this study. RACE scores will be used to re-categorise participants as LVO present or absent based upon a published cut-off value.(iii)Exploratory subgroup analysis: if data permit, this will be carried out by graphical presentation of the CBA results. The proposed subgroups to investigate are:
Acute stroke: patients with a diagnosis of acute stroke will be evaluated (i.e. after exclusion of patients with PTS, TIA and mimic conditions).Acute IS: patients with acute ischaemic stroke will be evaluated (i.e. after exclusion of patients with TIA, mimic conditions, PTS and haemorrhage).Exclusion of participants having posterior circulation stroke: participants with posterior circulation stroke, defined by the Oxford Community Stroke Project (OCSP) classification and verified against relevant NIHSS components will be excluded. Clinically, these individuals would be considered unlikely to have anterior circulation vessel occlusion or haemorrhage, and might not have a CBA reading performed as part of their emergency assessment. The remaining population will be evaluated.

Further exploratory analyses may be undertaken but these analyses will be data-driven and reported as such.
4.Objective 4: To report the technical failure rate of the CVS.

Technical and clinical reasons will be reported for why a CBA reading was attempted but not obtained. Technical reasons will include device failure resulting in no data acquisition, and collection of erroneous raw data leading to calculation of a CBA value which is perceived to have an implausible bioimpedance pattern.

Data from the following groups will be reported but excluded from the analyses:

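### Exploratory Objective 3(ii) uses RACE as a reference diagnosis for LVO, so it measures CBA's agreement with a clinical scale, not its accuracy for LVO

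*Protocol article*

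**What the plan says.** The Reference standards section sets LVO by blinded neuro-radiologist reading of CT/MR angiography: "LVO defined as a Ten Point Clot Burden Score <10". It gives the reason: "Whilst brain imaging tests are available which objectively confirm any intracerebral haemorrhage (CT), LVO (CT/MR angiography), and PTS (CT".

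In the Statistical analysis section, Objective 3(ii) repeats the Objective 1 modelling of CBA under alternative definitions of LVO, "where the reference diagnosis will be assigned as follows". Two are listed. One is a revised radiological definition, should clinical consensus change. The other is RACE, introduced with the statement that currently "the most accurate clinical scale for the indication of the presence of LVO is the Rapid Arterial oCclusion Evaluation (RACE". On its source: "A numerical RACE score will be calculated retrospectively using the hospital NIHSS (which contains all score items". On its use: "RACE scores will be used to re-categorise participants as LVO present or absent based upon a published cut-off value".

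The status of the whole objective is stated: "This is an exploratory objective, and as such the analyses will be data-driven and dependent on results for objectives 1 and 2".

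**The concern.** As worded, RACE supplies the outcome variable in the CBA model. It is neither a competing test nor a covariate. A participant with a mimic or a haemorrhage who scores above the cut-off becomes LVO present despite the imaging. A participant with angiographic LVO who scores below it becomes LVO absent. CBA is then marked wrong where it is right and RACE is wrong, and marked right where both share the same error.

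The output would be labelled diagnostic accuracy for LVO without being that. The Objective 1 procedure also estimates a new CBA threshold when the acceptance criteria are missed, so this analysis could produce a cut-off tuned to RACE and not to occlusion.

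The choice also sits badly with the article's other rules. The section on expert clinician diagnosis says that the 72-hour clinical diagnosis does not define LVO, and that imaging prevails when it disagrees with a clinical diagnosis of TIA or mimic. A score built from admission signs would reverse that order.

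**Working it through.** **Reading the text.** RACE fills no gap in the reference. Ischaemic strokes without CT/MR angiography are already excluded from the analyses of operating characteristics, so every analysed ischaemic stroke has an angiographic LVO status. For these participants RACE replaces a better reference that is available.

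**Inputs.** The article gives no figure for this analysis, so there is none to reproduce.
- LVO frequency p = 0.27 and analysable N = 112 (Sample size).
- Acceptance criteria: sensitivity at least 70%, specificity at least 80% (Statistical analysis, Objective 1; carried to LVO by Objective 2).
- RACE sensitivity (Se) and specificity (Sp): not given. Assumed, over a range.

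**A CBA test that agrees perfectly with angiography, scored against RACE.**
- Apparent sensitivity = PPV of RACE = p·Se / [p·Se + (1−p)(1−Sp)]
- Apparent specificity = NPV of RACE = (1−p)·Sp / [(1−p)·Sp + p(1−Se)]

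For RACE 85/70, apparent sensitivity is 0.2295 / (0.2295 + 0.2190) = 51%, and apparent specificity is 0.5110 / (0.5110 + 0.0405) = 93%.

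| Assumed RACE Se/Sp | Apparent sensitivity | Apparent specificity |
|---|---|---|
| 60/60 | 36% | 80% |
| 85/70 | 51% | 93% |
| 80/80 | 60% | 92% |
| 70/85 | 63% | 88% |
| 85/85 | 68% | 94% |
| 90/90 | 77% | 96% |
| 95/95 | 88% | 98% |

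In counts, for RACE 80/80 and N = 112: 30.2 participants have LVO and 81.8 do not. RACE calls 24.2 + 16.4 = 40.5 positive (rounded). The perfect CBA test is positive in 24.2 of these, which is 60%. Against angiography it would score 100%/100%.

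**When does the perfect test reach 70% apparent sensitivity?** Solving for Sp gives Sp ≥ 1 − (0.30/0.70)·p·Se/(1−p). At Se 0.85 this is 1 − 0.4286 × 0.2295/0.73 = 0.865, so about 87%. At Se 1.00 it is 84%, and at Se 0.60 it is 91%.

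**Dependence on p.** With p assumed to be 0.35, RACE 85/70, 80/80 and 70/85 give apparent sensitivities of 60%, 68% and 72%.

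**A good but imperfect CBA test.** Take true sensitivity and specificity of 85%, the values in the Sample size section, and assume its errors are independent of RACE errors given true LVO status. Apparent sensitivity is then 0.85·PPV + 0.15·(1−PPV), and apparent specificity is the same expression with NPV. The results (sensitivity/specificity) are:
- RACE 70/80: 54.5%/76.5%
- RACE 85/70: 50.8%/79.9%
- RACE 85/85: 62.4%/80.7%
- RACE 90/90: 68.8%/82.2%

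Such a test meets both criteria against angiography, but misses the sensitivity criterion against RACE in all four cases.

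**The case against.** The strongest reply is that little depends on this analysis. It is one of two definitions in one part of an exploratory objective. Objectives 1 and 2, the validation of the threshold of 10 and the sample size all keep the imaging-based reference. This stands, and it limits the severity.

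A reader might infer several stronger things that the article does not support:

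- **That CBA is never set beside clinical severity against angiography.** Objective 3(i) adds clinical variables, NIHSS among them, to CBA with LVO as the outcome, and the article says the NIHSS holds all RACE items. Combined performance is therefore partly explored. What is absent is a direct comparison of CBA with RACE against angiography.
- **That the Background section disowns RACE.** Its remark that "their performance in practice does not support widespread introduction" concerns assessments completed by paramedics. RACE here comes from the hospital NIHSS, so this is context and not a direct contradiction.
- **That a perfect CBA test must fail.** That depends on unstated RACE accuracy and on prevalence. At 90/90 or 95/95 the perfect test passes, and at p = 0.35 so does the 70/85 case. The LVO share of the analysed set may differ from 27%, because ischaemic strokes without angiography are left out.
- **That CBA would look poor throughout.** For a perfect test the loss falls on sensitivity. Apparent specificity, on which the study is sized because the intended use is to rule in, stays at or above 80% over the whole range tried.

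None of this makes RACE a reference standard. At any RACE accuracy short of perfect, a perfect CBA test cannot score 100%/100%.

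**Conclusion.** The point holds for the RACE definition in Objective 3(ii). As written, the analysis estimates agreement with a clinical scale and would report it as diagnostic accuracy for LVO, possibly with a re-estimated CBA threshold.

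At 27% LVO and assumed RACE sensitivity/specificity from 85/70 to 90/90, a perfect test would show about 51% to 77% apparent sensitivity. It would fall below the 70% criterion unless RACE specificity were about 87% or more (at RACE sensitivity 85%). These sizes are illustrations under assumed RACE accuracy. For a real device whose errors are correlated with those of RACE, the direction of the bias cannot be predicted.

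Severity is moderate to minor. It would be wrong to conclude that the study's main accuracy results are compromised, because Objectives 1 and 2 do not use RACE.

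**What to change.** Remove RACE from the list of alternative reference diagnoses in Objective 3(ii); the radiological alternative can stay. Analyse RACE at the published cut-off as a comparator index test, in the same participants and against the same LVO reference as Objective 2. Report paired differences between CBA and RACE in sensitivity, specificity and AUC, with confidence intervals. If a CBA-versus-RACE table is kept, call it agreement, apply no accuracy criterion to it and derive no CBA threshold from it.

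The cost is a change of wording, since NIHSS component scores and angiography findings are already collected. The one drawback is precision. About 0.27 × 112 = 30 LVO cases are expected, so each case moves sensitivity by about 3.3 percentage points (1/30). The paired sensitivity comparison will be imprecise and should be reported as exploratory.

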### Study participants

Trained hospital staff (e.g. research nurses, research trained doctors) will attempt a CBA measurement with the CVS on patients that fulfil the following criteria:

Inclusion criteria:
Aged 18 years or overTransportation to the study hospital by ambulanceNew stroke suspected by ambulance personnel before hospital arrivalAt least responsive to tactile stimuli on hospital arrival—i.e. A, V or P on the Alert Voice Pain Unresponsive (AVPU) scale.Routine emergency brain imaging is intended to be performed within 60 min of hospital arrival or has already been performed within 60 min of hospital arrivalA CBA reading can be attempted +/− 30 min of the first routine emergency brain imagingThe CBA reading can be attempted within 6 h of a hospital stroke specialist last known well time or symptom onset time.

Exclusion criteria:
Females who are pregnant, lactating or at risk of pregnancy (i.e. who are not surgically sterile or at least 1 year post last menstrual period). If this information is unknown/cannot be rapidly established, females < 56 years of age will be excluded.Already assessed at another hospital and transfer to the regional neurosciences centre is for further investigation or treatmentHypoglycaemia (capillary glucose < 3.5 mmol/l)Presence of any known implanted electro-stimulating devices in the head and neckPresence of implanted hearing aids (removable hearing aids should be taken out before use of the CVS)Presence of any known metallic craniofacial implants, such as bone fixation plates (aneurysm coils or clips are acceptable) or cranioplastyRecent craniotomy, craniectomy or other reason known for the presence of intracranial airPhysical inability to wear the investigational device (e.g. skin lesion on scalp, haematoma)Any other condition, which in the judgment of the stroke clinician might prevent the patient from tolerating CBA measurement or brain imaging (e.g. severe agitation or requiring immediate intensive treatment unit admission).Ambulance staff suspected stroke but hospital staff do not consider that brain imaging within 60 min of hospital arrival is a required investigation (e.g. a different diagnosis is made with other routine assessments or tests shortly after admission)

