### Blinding

Patients, clinicians and hospital research staff will be blinded to CBA results. Neuro-radiologists responsible for providing the independent imaging reports and research clinicians responsible for the outcome state attribution process will also be blinded to CBA results. In addition, staff from Cerebrotech Medical Systems Inc who will provide CBA readings from raw measurement data will not have access to any clinical data prior to provision of a CBA reading.

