Participants with ischaemic stroke but without CT angiography or MR angiography, as their LVO state is unknown.Participants with an expert clinician diagnosis of ‘unclear’ which cannot be resolved as it has not been possible to assign a diagnosis.Following attendance at the hospital, other information sources may reveal retrospectively that one or more of the study eligibility criteria have not been met (e.g. the symptom onset was more than 6 h ago). This is not uncommon during emergency care assessments due to the accuracy of information immediately available. Participants who do not meet the inclusion criteria according to information available by 72 h after admission will not contribute towards the analyses.Participants where a CBA reading is attempted but this is unsuccessful (the CVS alerts the operator to failure to capture data).All CBA readings obtained will be checked for a plausible bioimpedance pattern. Participants with CBA readings who are perceived to be implausible will not be included in the analyses, e.g. readings obtained from patients with previously unknown cranial metallic implants.

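### Sensitivity is judged only among accepted CBA readings, which overstates detection among all patients tested, and the plausibility check that decides acceptance has no fixed criterion, assessor or blinding

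*Protocol article*

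**What the plan says.** The end of the Statistical analysis section of the protocol article lists several groups under the rule "Data from the following groups will be reported but excluded from the analyses". Two of them concern the index test.

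- Failed attempts: "Participants where a CBA reading is attempted but this is unsuccessful".
- Rejected readings: "All CBA readings obtained will be checked for a plausible bioimpedance pattern", and then "Participants with CBA readings who are perceived to be implausible will not be included in the analyses". The single example is "readings obtained from patients with previously unknown cranial metallic implants".

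Objective 4 counts both groups in the technical failure rate and reports reasons. The same section accepts the threshold of CBA = 10 if specificity is at least 80% and sensitivity at least 70%. If that fails, a new threshold is chosen to maximise specificity while holding sensitivity at about 70%.

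The Sample size section gives the intended use: ruling patients in for redirection to a neuroscience centre. It also allows more participants to be sought if too few can contribute to the analyses.

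On blinding, the Blinding section says that manufacturer staff "will not have access to any clinical data prior to provision of a CBA reading". The Study design and index test sections say the same in substance. Imaging reviewers and those attributing outcome states are blinded to CBA. None of these sections mentions the plausibility check.

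**The concern.** The 70% criterion describes patients for whom the device worked and whose reading was accepted. A service using the test to redirect patients needs to know how many complex strokes it would pick up among everyone on whom it is tried. If a non-result leads to no redirection by the test, it acts as a negative result, and every case without an accepted reading is a missed case that the accuracy table never shows. Recruiting further participants to reach the analysable number replaces those cases with successful readings.

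The loss may also be related to the condition. The reasons recorded for an abandoned reading include agitation and a change in the patient's condition. The article gives no rates by diagnosis, so this is a possibility only.

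The second part is the acceptance decision itself. Plausibility is a matter of perception, with no stated criterion, assessor or time point. It is applied to readings already obtained, whereas the manufacturer's blinding is stated only up to provision of the reading. With few cases, a handful of discretionary rejections can move sensitivity visibly.

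**Working it through.** **The plan's own figures.** The Sample size section gives frequencies of 27%, 3% and 4%, so complex stroke is 34% and non-cases are 66% (73% for LVO alone). Testing a specificity of 85% against 70% with a one-sided alpha of 0.05 and 90% power needs 73 non-cases by the exact binomial method. That gives 73/0.66 = 110.6 and 73/0.73 = 100 participants, close to the stated 112 and 101. The 10% inflation gives 112 × 1.1 = 123.2 or 112/0.9 = 124.4, against the stated 124. These figures are not in dispute. The 10% covers every exclusion group together (no angiography, unresolved diagnosis, late ineligibility, failed and implausible readings), so it is only a reference point for f.

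**Inputs.**

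- Sensitivity among accepted readings: 85% (Sample size section) and 70% (acceptance criterion). The 70% row also matters because a re-estimated threshold would aim for that value.
- f, the share of cases without an accepted reading: not given. Assumed 5%, 10% and 15%.
- Convention: a non-result counts as test-negative. This is an assumption about use, because the article does not say what would follow a failed reading.

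**Formulas.**

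- Detection among all attempted = sensitivity among accepted × (1 − f).
- Sensitivity among accepted needed to detect 70% of all attempted = 70%/(1 − f).
- Specificity among all attempted = 1 − (1 − specificity among accepted) × (1 − f), with f now the share of non-cases.

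**Sensitivity.**

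| f | 1/(1−f) | 85% becomes | 70% becomes | Needed among accepted for 70% of all attempted |
|---|---|---|---|---|
| 5% | 1.053 | 80.8% | 66.5% | 73.7% |
| 10% | 1.111 | 76.5% | 63.0% | 77.8% |
| 15% | 1.176 | 72.3% | 59.5% | 82.4% |

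For example, 0.85 × 0.90 = 0.765 and 0.70 × 0.90 = 0.630. A sensitivity of 85% falls to 70% only when f = 1 − 0.70/0.85 = 17.6%.

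**Specificity.** At f = 10%, 1 − 0.15 × 0.90 = 86.5% in place of 85%, and 1 − 0.20 × 0.90 = 82.0% in place of 80%. It rises slightly under this convention.

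**In patients.** If all 124 were eligible with a known outcome state, about 124 × 0.34 = 42.2 would be complex-stroke cases. At 85% among accepted readings, four cases without one give 0.85 × (42.2 − 4)/42.2 = 76.9%, or about 2 points per lost case.

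**The plausibility step against the blinding text.** There are two possibilities. If the manufacturer checks the pattern before returning the value, the stated blinding covers the check. If anyone checks after the value is returned, no stated rule covers it: the manufacturer's blinding has ended, and the other rules protect reference-standard assessors from CBA, not index-test assessors from the reference data. The research group that receives the readings also maintains the clinical database, and the article states no lock of accept/reject decisions before linkage. The text does not say which possibility applies.

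**The case against.** The strongest reply is about the estimand. Objectives 1 and 2 ask how accurate the measurement is, and a patient without a reading has no measurement. Counting non-results as negative answers a pathway question. Some abandonments, such as too little time before imaging, may belong to this hospital setting and would understate pre-hospital performance. This stands as a reason to make the all-attempted analysis supplementary and not the sole basis for the 80/70 decision. It does not make the accepted-reading figure a measure of detection among those tested.

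The exclusions are also disclosed, and Objective 4 reports them. That is true, but an overall failure rate cannot correct sensitivity. Failures by outcome state are needed, and the article promises only reasons.

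Signal criteria and a decision lock could sit in the full protocol or SAP, neither of which is shown. That is fair for the detail. The exclusion rule, however, is fixed in the article, and so is its subjective wording.

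Four stronger readings are tempting and not supported:

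- *That plausibility is judged unblinded.* The step is unspecified, and a check before the value is returned would be blinded.
- *That scans are used to discard readings which disagree with them.* This could be inferred from the implant example, but the article does not say how such an implant comes to light. When known, the same feature is an exclusion criterion ("Presence of any known metallic craniofacial implants, such as bone fixation plates"), so the example looks like late-discovered ineligibility. Disagreement with imaging is nowhere a criterion.
- *That the test would miss the 70% criterion once exclusions are counted.* At the planned 85% it stays above 70% for f from 5% to 15%. A fall below needs a lower sensitivity or a larger f. For instance, 75% falls below once f exceeds 1 − 0.70/0.75 = 6.7%, but 75% is not a figure in the plan.
- *That specificity, on which the study is sized, is inflated too.* It is not.

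**Conclusion.** The point holds in two limited parts. First, by excluding failed and implausible readings, the plan judges its sensitivity criterion on accepted readings alone. For the rule-in use this overstates detection among all tested by 1/(1−f): about 4 to 13 percentage points at 85% (85 − 80.8 to 85 − 72.3) and 3.5 to 10.5 at 70%, for f between 5% and 15%. These sizes rest on an assumed f and on treating a non-result as negative. Second, the criterion, assessor, timing and blinding of the plausibility check are not fixed, so the article does not secure that rejection is independent of the reference data. It also gives no evidence that rejection would be dependent on them. The sample size and the specificity target are unaffected. This should be corrected before the data are linked.

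**What to change.** 1. Define implausibility by preset criteria on the raw signal. Name who applies them, require that person to be blind to clinical, imaging and outcome data, and lock the accept/reject list before linkage. Handle an implant discovered later as an eligibility matter, separately from signal plausibility.
2. Tabulate failed and implausible readings, with reasons, by outcome state.
3. Add a supplementary analysis of all eligible attempted readings with an attributable outcome state, counting non-results as test-negative. Report it beside the accepted-reading analysis when the 80/70 criteria are interpreted, and do the same for any re-estimated threshold.

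The Participant identification and consent section already seeks enrolment of patients whose reading failed for technical reasons, so reference data can be available without new procedures or extra patients. The cost is some wording, one additional table and a somewhat lower sensitivity figure beside the main one.
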